### Withdrawal of subjects

Participants have the right to withdraw from the trial at any point, for any reason, without prejudice to future care. This is clearly stated at time of consent. The investigator can also withdraw participants from the study intervention in the event of protocol violations or if it was felt that involvement in the service was adding unnecessary burden or distress (eg, if participant was approaching end of life). Participant withdrawals will be included within the study analyses and reporting.

Participants may opt to limit the number of interactions—for example, daily questionnaires, that they undergo, if these are burdensome. They may also request ‘conventional’ scheduled face-to-face clinical review rather than remote managed review at any time point. This will be accommodated as outpatient or inpatient attendances, within routine clinical timescales as judged appropriate by the clinical team, in line with current service provision.

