#### Follow-up clinical data

Smoking cessation, vaccination status, pulmonary rehabilitation, COPD comorbidity, COPD exacerbation history, COPD medications and other treatments, inhaler technique and narrative history will be updated at clinical encounters, as relevant.

A data feed from NHS GG&C Trakcare platform to RECEIVER Study COPD platform will present information on hospital attendance and admissions.

Clinical episodes are also captured in the weekly PRO questionnaires, and manually inputted by the clinical team, when these are noted.

Accuracy of coding of clinical summary data and clinical episodes will be reviewed in a proportion of recruited participants, by a respiratory physician working independent of this study.

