### Data from PROs

Participants (or their family or carer) will complete PRO questionnaires in the patient web portal. Daily SMS and/or email notifications are provided as a prompt to complete these. There is support information in the associated website to assist participants with any difficulties with the patient portal. Additional support will be provided by the clinical users if required.

Participants will complete symptom diary and COPD assessment tool (CAT) questionnaire daily. Medical Research Council dyspnea score (MRC) and healthcare episode questionnaires will be completed weekly. EQ-5D-5L generic quality of life questionnaire will be completed every 4 weeks. These questionnaires have been integrated to improve question flow and simplify the user experience. Questionnaire flow content is included in the online supplemental material 1.

10.1136/bmjresp-2021-000905.supp1Supplementary data

PRO data are presented unmodified, in a ‘user-friendly’ format (co-designed with clinical users), in the clinician dashboard. These unmodified data will inform and enhance clinical encounters and patient–clinician communication.

Pilot user experience research shows that the daily PRO questions can be completed in ~70 s, with weekly questions taking an additional 90 s, and monthly generic quality of life questions taking an additional 5 min.

Specific permission for use of CAT questionnaire within this e-health system has been obtained. The use of other PROs is covered by available open licensing.

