## Study outcome measures

Primary and secondary endpoints for the RECEIVER Study are shown in table 1.

**Table 1 T1:** RECEIVER primary and secondary endpoints

Primary endpoint	Proportion of enrolled high-risk participants with COPD who use remote management in a digital service model
Secondary endpoints	Clinical outcomes, comparing impact of digitally enabled remote management versus historical and contemporary SafeHaven cohorts: Clinical events: COPD exacerbation; unscheduled care contact (digital platform, COPD team visit, primary care, emergency department, hospital admission); mortality—COPD and non-COPD related. Hospital occupied bed days preceding and subsequent 12 months (adjusted time interval if survival <12 months). Treatment uptake (where indicated): smoking cessation; pulmonary rehabilitation; vaccination; supported self-management; home oxygen; home NIV. NIV group: NIV usage, symptom change, NIV therapy parameters, blood gases during routine clinical care. Supported self-management: utilisation of self-management information (page views), number of exacerbation managed at home versus in hospital, number of rescue packs used in 12 months (captured through weekly PROs), utilisation of messaging (number of message threads), sputum microbiology (where available during routine clinical care), impact of patient activation measures (where measured during routine care). Impact of demographics, physiology and patient activation measures (where measured during routine care)—deprivation category of area of residence, age and sex, number of previous admissions, smoking status, participation in pulmonary rehabilitation in previous 2 years; lung function measurements, modelled home air pollution exposure; EMG, oscillometry and home air pollution monitoring in subset of participants where this is carried out—on outcomes, clinical events and treatment uptake. Clinical service outcomes for digital service model, remote-managed home NIV and supported self-management: Remote-managed home NIV: number, nature and complexity of NIV therapy reviews and interventions to provide. Supported self-management: number, nature and complexity of reviews and interventions to provide. Digitalised service model: user and developer time/cost required for development and modification of clinical dashboard; qualitative analysis (clinical user satisfaction and reflection on efficiency or additional workload); quantitative analysis (clinical dashboard utilisation tracking). Patient portal: user and developer time/cost required for development and modification of clinical dashboard; qualitative analysis (user satisfaction) and quantitative analysis (uptake, engagement with app and wearable, successful use of digital service vs bypass to conventional healthcare contacts). Machine learning-supported exploratory analyses of associations and relative predictive importance of electronic health record, PROs, wearable physiology and NIV parameters: Associations between changes in PROs (MRC, CAT, symptom diary, and EQ-5D-5L questionnaires) with routine clinical care interventions, COPD exacerbation and other clinical events. Associations between changes in wearable monitoring parameters (activity, sleep, heart rate variability, energy expenditure, respiratory rate) with routine clinical care interventions, COPD exacerbation and other clinical events. Associations between changes in NIV-monitored parameters (usage, leak, airway pressures, respiratory rate, tidal volume, minute ventilation, inspiratory/expiratory ratio and detected respiratory events) with routine clinical care treatment interventions, COPD exacerbation and other clinical events. Associations between changes in clinical endpoints and relative importance plots of all remote management-acquired data (including EMG, oscillometry and home pollution monitoring exploratory endpoints in subgroup these measured on) to determine contribution of these to outcome prediction, and therefore value of these for future prospective study. Patient-centred outcomes: Health-related quality of life (EQ-5D-5L) at baseline and monthly during study. Qualitative user research (planned subset of participants, convenience sample) with semistructured user experience interviews. Impact of patient activation (where this is measured at baseline and/or follow-up during routine clinical care) on enrolment and use of digital service model. Healthcare cost analyses: Development and installation costs for digitalised service model for remote management of COPD. Recurring costs (clinical staffing, digital platform hosting, digital platform scheduled update and maintenance) for digital service model for remote management of COPD. Projected direct and indirect cost-savings (admission and unscheduled care reduction, travel, carer burden impact, clinical efficiency) of high-risk COPD with digitally enabled remote management, compared with previous service model.

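### Rescue-pack use, and in part home-managed exacerbations, are counted through voluntary weekly questionnaires while hospital events are not, so the 12-month counts can understate home management in low completers

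*Protocol article*

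**What the plan says.** In the protocol article, Table 1 (Study outcome measures) includes among the supported self-management endpoints "number of exacerbation managed at home versus in hospital, number of rescue packs used in 12 months (captured through weekly PROs"). The source note in brackets follows directly on rescue packs.

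The questionnaire that carries these events is weekly (Data from PROs): "Medical Research Council dyspnea score (MRC) and healthcare episode questionnaires will be completed weekly". A family member or carer may complete it, and reminders are sent daily. Participants may reduce what they complete (Withdrawal of subjects): "Participants may opt to limit the number of interactions—for example, daily questionnaires, that they undergo, if these are burdensome".

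Hospital events have their own route (Follow-up clinical data): "A data feed from NHS GG&C Trakcare platform to RECEIVER Study COPD platform will present information on hospital attendance and admissions". The same section gives a further source for episodes: "Clinical episodes are also captured in the weekly PRO questionnaires, and manually inputted by the clinical team, when these are noted". It also says that several clinical items, exacerbation history among them, are refreshed when the patient is seen; the sentence ends "inhaler technique and narrative history will be updated at clinical encounters, as relevant".

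The Primary endpoint measures section makes PRO completion part of how use of the service is judged, with a target of at least one PRO set per participant per week. No expected completion rate is given.

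**The concern.** The two sides of the home-versus-hospital comparison are ascertained by different mechanisms, and only one depends on the participant's engagement. For rescue packs, the weekly questionnaire is the only source that the article names. Completion is itself a study outcome, so the trial cannot take it to be full when it counts events.

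Three things are at stake within the RECEIVER cohort, apart from any difference in capture between participants and controls:

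- Low completers would appear to use fewer rescue packs and to manage fewer exacerbations at home.
- If completion changed during the 12 months, the counts would change with it even if the disease did not.
- The Statistics and data analysis section plans correlations and group comparisons of clinical endpoints against supported self-management parameters. If reported events rise with completion, more engaged participants would seem to have more exacerbations purely because more of theirs are recorded.

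Table 1 does adjust for exposure elsewhere: bed days carry a shorter interval for participants who survive less than 12 months. The self-management counts carry no adjustment of either kind.

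**Working it through.** The article gives no event rate, completion rate or power figure for this endpoint, so there is no stated figure to reproduce. What follows is an illustration on assumed inputs.

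**Inputs (all assumed).** Three home-managed events and one hospital event per patient-year, a true home share of 3/4 = 75%. *c* is weekly completion, unrelated to events. *m* is the share of home events in missed weeks that is recovered by clinician entry or by later recall. Hospital events are taken as fully captured, for simplicity.

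**Formula.** Captured fraction s = c + (1 − c)m. Observed home share = 3s/(3s + 1).

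| Completion c | m = 0 | m = 0.6 |
|---|---|---|
| 90% | 2.7/3.7 = 73% | 2.88/3.88 = 74% |
| 70% | 2.1/3.1 = 68% | 2.64/3.64 = 73% |
| 50% | 1.5/2.5 = 60% | 2.4/3.4 = 71% |

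**Other true shares.** At 50% completion, with true home shares from 50% to 80%, the error runs from −17 to −13 percentage points with m = 0, and from −6 to −4 with m = 0.6. With full completion or full recovery it is zero.

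**Change over time.** Suppose completion fell linearly from 90% to 50% over 52 weeks. The quarterly means of c would be 0.853, 0.751, 0.649 and 0.547. With m = 0 the observed share would be 72%, 69%, 66% and 62%; with m = 0.6 it would be 74%, 73%, 72% and 71%. The true share is 75% throughout. On the same path mean completion is 70%, so three true rescue packs a year would be counted as 3 × 0.70 = 2.1 with no recovery.

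**Link with engagement.** Two participants each have three true home events, one completing 90% of weeks and the other 50%. With m = 0 they show 2.7 and 1.5 events, a ratio of 1.8. With m = 0.6 they show 2.88 and 2.4, a ratio of 1.2.

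**Check of a rate.** If each questionnaire covers only its own week and completion is unrelated to events, the expected count is 3c over 52c completed weeks. That is 3/52 per week, or 3 per year at any c. If the recall window reaches back over missed weeks, that denominator is too small: at c = 50% with full recovery, 3 events over 26 completed weeks annualise to 6. The denominator must then be the time that the recall window covers.

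**Check of restricting the split to completed weeks.** Suppose completion is 70% in weeks with a home event and 30% in weeks with a hospital event (assumed). The restricted share is 2.1/(2.1 + 0.3) = 87.5%, an error of +12.5 points. The unrestricted count gives 2.1/3.1 = 68%, an error of −7 points.

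**The case against.** A reader might infer that home-managed exacerbations are counted from weekly questionnaires alone, against a complete hospital feed, so that the split is certainly biased and will drift. The article does not support that.

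- The weekly-PRO note attaches to rescue packs. For exacerbations the article also names clinician entry and updates at clinical encounters (Follow-up clinical data), and the clinician dashboard as a source record (Source data). Secondary endpoint measures adds the SafeHaven export, the Trakcare feed and platform tracking. Episode coding is independently reviewed in a proportion of participants.
- The article does not call the hospital feed complete, and it does not say that a skipped week is scored as no event. How missed weeks are handled may be set out in a fuller document, so silence on that is no fault here.
- No completion rate or decline is documented. Daily prompts and completion by carers support response, and the example of limiting interactions is the daily set, not the weekly one.
- The questionnaire content is in a supplement that is not shown. If the item asks about the time since the last entry, much of the loss is recovered.
- The study is an unpowered feasibility study that acknowledges its risk of bias, and under-counting home events works against the service on the home share.

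All of this stands, and it limits the certainty and size of the point. It does not remove it. Clinician entry depends on an episode being noticed, the coding review is partial, and none of the other listed sources is stated to record a self-treated episode at home. For rescue packs no second source is named. The permission to limit interactions is general, with the daily set only as an example.

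**Conclusion.** The point holds in a limited form. Rescue-pack use is fixed as a 12-month number captured through voluntary weekly questionnaires, and home-managed exacerbations rest partly on the same source, while hospital events do not. The counts are prone to understate rescue-pack use and home management in participants who complete less. They could shift if completion shifts, and could associate engagement with event counts through measurement alone.

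The size cannot be determined from the article. At an assumed 50% completion and a true home share of 75%, the shortfall in the home share is about 15 points with no recovery and about 4 with 60% recovery. It vanishes with full completion or full recovery. These figures assume that skipped weeks are unrelated to events and that hospital events are fully captured. Severity is minor: a secondary endpoint in a feasibility study.

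**What to change.** Alongside the raw 12-month counts:

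- Report rescue packs and questionnaire-reported home exacerbations as rates per completed questionnaire-week, or per period covered if the recall window is longer than a week.
- Report weekly completion beside these rates, overall and over time.
- Keep hospital events over all follow-up time.

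Do not make a home-versus-hospital split restricted to completed weeks the main analysis. Admitted patients may complete less, so the restriction could discard known admissions and inflate the home share. The SafeHaven medication history (EHR data) can serve only as a rough cross-check on supply, since it is not stated to record rescue-pack use.

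The cost is analysis wording only, because completion is already tracked for the primary endpoint. The downsides are wider intervals for low completers, and that the rate still assumes completion is unrelated to events.

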### Primary endpoint measures

The proportion of participants who use the digital service model will be determined from screening versus recruitment log, and with participant usage (PRO completion, wearable usage, home NIV usage and digital service contacts vs conventional healthcare contacts), monitored using consented platform tracking analytics. A target of submission of at least one PRO set per participant per week will be used to ascertain utilisation measures.

### Secondary endpoint measures

Clinical events, hospital occupied bed days, treatment uptake, NIV usage and therapy, incidences of supported self-management and the impact of demographics on these will be captured within the digital service platform with data from weekly SafeHaven export, Trakcare real-time episode data feed and platform tracking analytics.

The process evaluation metrics for the digital service model will be captured by platform tracking analytics, project delivery process documentation and supplementary user experience research conducted as part of the digital service project delivery.

Machine learning-supported analysis of study dataset will be conducted post hoc.

Patient-centred outcomes will be captured within RECEIVER patient portal.

Qualitative user experience research will be undertaken with a subgroup of participants to inform implementation strategy and will be presented as a descriptive summary. A sample of convenience will be taken from within the RECEIVER cohort. Semistructured interviews will be conducted, and thematic analysis will be performed. Interview transcripts will be coded, and the codes used to generate themes. Discussion of the themes within the research team will be conducted to ensure agreement and add rigour.

Cost analysis will be based on audited accounts for the RECEIVER innovation project delivery, combined with standard NHS tariffs, NHS Scotland medical/agenda for change salary scales and indirect costs from standard burden of COPD cost projections.

## Data management

The study data file will be held in a locked cabinet in the Department of Respiratory Medicine, Queen Elizabeth University Hospital, Glasgow, with an electronic copy securely stored on the EDGE Clinical Research Management System. All electronic data and COPD service digital architecture (including machine learning algorithms) will be held within NHS GG&C e-health systems, with industry standard security and identity assurance processes. The core components of the digital service will be held within NHS GG&C Azure cloud tenancy, further ensuring security and identity assurance, and avoiding the need for data de-identification prior to machine learning analysis.

Data access will be password protected and accessible only by study investigators, with data management as per NHS GG&C and NHS Scotland data protection policies. Platform analytics will track user interactions and data changes, to provide an audit trail for data integrity.

At study completion, the comprehensive study dataset will be submitted for inclusion in NHS GG&C SafeHaven. This will allow (with appropriate SafeHaven standard operating proceedures (SOP) and Local Privacy and Advisory Committee (LPAC) application approvals) subsequent de-identified review of all study outcomes, reanalysis of the dataset, and contribution of the dataset to future COPD data linkage and other research work within NHS Scotland.

## Statistics and data analysis

Secondary outcomes in the RECEIVER observational cohort will be compared with matched retrospective data from de-identified linked datasets of historical control and contemporary control high-risk patients with COPD. These will comprise of patients identified from coding and admission data as having had severe exacerbation of COPD between 1 January 2010 and 30 April 2019 (historical cohort) and between 1 July 2019 and 30 June 2020, excluding participants enrolled in the RECEIVER Study (contemporary control). The historical control dataset will contribute to machine learning models development. Secondary outcome analysis will be separately compared between the RECEIVER cohort, historical cohort and contemporary control cohort. This component of the study is also separately registered with dataset access approval from NHS GG&C SafeHaven LPAC.

The clinical endpoint data will be reported as a proportion and 95% CI for that outcome, calculated by Kaplan-Meier method. Demographic data will be presented as mean and SDs, or medians and IQRs as appropriate. Correlation, t-test, analysis of variance and effect size analyses will be used as appropriate for secondary endpoint analysis, comparing results of clinical endpoint and patient-centred outcomes with NIV therapy and supported self-management parameters.

Machine learning ensemble methods will be used to develop binary classification problems for patient risk. Precision, recall, accuracy and C-statistics of the receiver operating characteristic curve will be used to evaluate model performance.

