## Study methods and analysis

### Study design

This study is a prospective observational cohort hybrid implementation and effectiveness study.^26^ It will be performed according to the UK Policy Framework for Health and Social Care Research (2020).^27^ The clinical intervention component is regarded as a phase IV adoption study. Data visualisation to facilitate guideline-based care, supported self-management and home NIV are evidence-based COPD interventions.

In this study, we will evaluate the adoption of digitally integrated remote management service innovations to support routine clinical care. Implementation of these will be evaluated and the digital innovations will be iterated to optimise them, based on user experience accrued during the study. We will acquire a consented dataset for trial endpoint analysis including exploratory machine learning-based predictive modelling. The machine learning analysis will also allow us to prioritise data inputs for follow-up study.

Secondary outcomes for the RECEIVER cohort will be compared with those from matched cohorts of patients acquired from the NHS GG&C SafeHaven dataset. Ethics approval is in place to access this large database of de-identified data, to establish a control cohort from a historical time series and a RECEIVER trial concurrent time series. These cohorts will be matched for demographics, COPD severity and hospital admission frequency with the RECEIVER cohort.

We will conduct a substudy of additional baseline and follow-up physiological measurements (oscillometry, parasternal electromyography (EMG), home pollution monitoring) in patients in whom it is feasible to obtain these during their hospital admission and/or hospital attendance alongside their routine clinical care.

Additionally, we will conduct a substudy of clinical users, with platform tracking analytics to measure clinician time spent on the platform, and user experience data. Clinical team members involved in the delivery of patient support using the digital service will be eligible for inclusion and appropriate consent will be sought. The qualitative components will be acquired through semistructured group or 1:1 interviews conducted by trained members of the research team. Thematic analysis will be performed. Anonymised transcripts will be coded, and themes generated from the codes. Themes will be discussed within the research team to reach agreement and add rigour.

An overview of the study design is provided in figure 2.

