### Study population

People with high-risk COPD attending secondary care in the North and South Sectors of NHS GG&C will be screened for inclusion in this study.

Inclusion criteria:

Confirmed diagnosis of COPD, established prescreening or at screening, defined as per Global Initiative for Chronic Obstructive Lung Disease (GOLD) 2020 guidelines.^6^Home NIV cohort: hypercapnic respiratory failure and/or sleep disordered breathing, meeting established criteria for provision of home NIV.Exacerbation cohort: presentation within last 12 months with severe or life-threatening exacerbation of COPD, defined as per GOLD 2020 guidelines.^6^Participant or close contact who has daily access to smartphone, tablet or home computer with internet access.Informed consent.>18 years of age.

Exclusion criteria:

Inability to comprehend informed consent.Communication barrier precluding use of COPD digital service.

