### Screening and eligibility assessment

Participants will be identified from ED attendance, hospital admission or COPD multidisciplinary team referral. It is anticipated that the majority of participants will be identified and recruited during their index acute admission.

Review of focused medical history and lung function test results will be undertaken as part of screening evaluation to ensure all inclusion and no exclusion criteria are met.

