## Data collection

### Data collection by research team

#### EHR data

The following data will be obtained from EHRs held within NHS GG&C SafeHaven: demographic, coded diagnosis list, Charlson Comorbidity Index, Scottish Index of Multiple Deprivation quintile, medication history, laboratory results, lung function results, ED attendance, hospital admission, pulmonary rehabilitation attendance data from 1 January 2010 onwards. These data will be presented for evaluation in a study machine learning analysis platform.

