#### Baseline clinical data

The following data will be collated when the participant is enrolled and added to the clinical details form visible on the clinician dashboard: participant age, sex, smoking status, vaccination status, comorbidities, COPD exacerbation history, COPD medications, lung function results, key laboratory results including maximal eosinophil count and modelled home pollution exposure (QCumber platform; NO2, O3, PM2.5, black carbon).

Participants who have not had contemporary spirometry (standard lung function test) will have this repeated at the time of recruitment—this would be routine clinical care.

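### Participants need GOLD-confirmed COPD, but controls are defined from coding and admission data with no stated confirmation of airflow obstruction, so the secondary clinical contrasts may be biased

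*Protocol article*

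**What the plan says.** For participants, the inclusion criteria (Study population) require: "Confirmed diagnosis of COPD, established prescreening or at screening, defined as per Global Initiative for Chronic Obstructive Lung Disease (GOLD) 2020 guidelines". Screening and eligibility assessment adds: "Review of focused medical history and lung function test results will be undertaken as part of screening evaluation". Baseline clinical data adds: "Participants who have not had contemporary spirometry (standard lung function test) will have this repeated at the time of recruitment".

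For controls, Statistics and data analysis gives the use and the case definition. The use: "Secondary outcomes in the RECEIVER observational cohort will be compared with matched retrospective data from de-identified linked datasets". The definition: "These will comprise of patients identified from coding and admission data as having had severe exacerbation of COPD". It applies to a historical window (1 January 2010 to 30 April 2019) and a contemporary window (1 July 2019 to 30 June 2020).

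Study design states how the groups are aligned: "These cohorts will be matched for demographics, COPD severity and hospital admission frequency with the RECEIVER cohort". The severity measure is not named.

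The EHR data section lists what SafeHaven can supply, including "medication history, laboratory results, lung function results, ED attendance, hospital admission, pulmonary rehabilitation attendance data from 1 January 2010 onwards". Lung function is therefore on the list, but no section makes it a condition for being a control.

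**The concern.** The two sides of each secondary clinical comparison enter through different diagnostic doors. The protocol's Introduction describes COPD as a disease of persistent symptoms with airflow limitation, and participants have lung function checked before they count as cases. A person whose admission was coded as a COPD exacerbation but who has no obstruction should fail RECEIVER screening, yet meets the control definition as written.

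Table 1 compares the RECEIVER cohort with these controls on exacerbations, unscheduled care, COPD and non-COPD mortality, bed days and treatment uptake. It also projects cost savings against the previous service model. If the control cohorts contain people with a different disease, part of any difference reflects who was admitted to each group, not the digital service. The historical dataset also contributes to machine learning model development, so the same records could enter model training.

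**Working it through.** **1. Figure to reproduce.** There is none. The 400 participants in Sample size rest on recruitment feasibility, and a power calculation is expressly declined. The protocol gives no predictive value for the control codes. The check is therefore a comparison of stated criteria, followed by an illustration with assumed inputs.

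**2. Criteria side by side.**

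| | RECEIVER participants | Historical and contemporary controls |
|---|---|---|
| Source of diagnosis | Confirmed to GOLD 2020, before or at screening | Coding and admission data |
| Lung function | Reviewed for eligibility | Held in SafeHaven; not stated as a criterion |
| Missing or old spirometry | Repeated at recruitment | Nothing stated |

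**3. Does matching close the gap?** Matching on COPD severity takes people already labelled as COPD and aligns them on a severity value. Because the measure is not given, the text does not show that a matched control has obstruction. Matching on admission frequency aligns prior use of hospital care. That should narrow a difference in later admissions, but does less for COPD-specific events, cause of death or treatment uptake.

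**4. Size, as an illustration.** Let PPV be the proportion of coded controls who truly have COPD, and *d* the mean annual admissions in coded controls without COPD minus the mean in controls with COPD. Then:

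shift in control mean = (1 − PPV) × *d*

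Neither input is in the protocol. I take PPV from 0.70 to 0.95 and *d* from −1 to +1.

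| PPV (assumed) | Misclassified per 400 controls | Shift at *d* = ±0.5 | Shift at *d* = ±1 |
|---|---|---|---|
| 0.95 | 20 | ±0.025 | ±0.05 |
| 0.90 | 40 | ±0.05 | ±0.10 |
| 0.80 | 80 | ±0.10 | ±0.20 |
| 0.70 | 120 | ±0.15 | ±0.30 |

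Worked line: PPV 0.70 and *d* = 1 give 0.30 × 1 = 0.30. The shift is zero if PPV is 1 or *d* is 0.

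The only yardstick in the protocol is the projected reduction of one admission per patient per year (Sample size). With 10-30% misclassified, the largest shifts are 0.10-0.30, or 10-30% of that reduction, in either direction. These are ceilings under the assumed inputs, because matching on admission frequency would tend to pull *d* towards zero.

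**The case against.** The strongest reply is that the article is silent on obstruction in controls but does not rule it out. The control component is separately registered, with its own dataset access approval, and code lists or diagnostic filters may be set there. Controls must have had a severe exacerbation and are matched on severity and admission frequency. The contrasts are secondary, in a feasibility study that disclaims definitive proof and acknowledges bias in general terms (Study limitations). Much of this stands, and it limits the weight of the point. It does not remove the point, because the article gives an affirmative case definition for controls and that definition differs from the one for participants. If the separate registration has a tighter one, the sponsor need only state it.

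A reader might infer three stronger things that the documents do not support.

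- **That controls are taken on codes alone and some certainly lack COPD.** The text says coding plus admission data, followed by matching, and gives no misclassification rate. The risk is plausible, not demonstrated.
- **That the error flatters the service by lowering treatment uptake in controls.** Table 1 restricts treatment uptake to patients for whom the treatment is indicated, so people without an indication should leave the denominator. The list also includes smoking cessation and vaccination, and nothing in the protocol suggests that uptake of these is nil in people without COPD. No direction can be assigned.
- **That the independent coding review makes the diagnosis firmer in participants.** It reads: "Accuracy of coding of clinical summary data and clinical episodes will be reviewed in a proportion of recruited participants". It covers only some participants, and concerns summary data and episodes. It is not stated to be a check of diagnosis.

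A further fair objection is that requiring prior spirometry in controls creates its own imbalance: untested controls would be dropped while untested participants are tested at recruitment. That stands, and it is why neither version of the control cohort should be reported alone.

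**Conclusion.** The point holds as a difference in stated diagnostic entry standards that may bias the secondary clinical contrasts by an unknown amount in either direction. The primary endpoint, the proportion using remote management, does not depend on the controls and is unaffected.

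For admissions, the illustrated ceiling of 0.10-0.30 per patient-year rests on two assumptions from outside the protocol: 10-30% of controls misclassified, and a difference of 1 admission per year between misclassified and true cases. It makes no allowance for matching. No comparable figure can be supported for treatment uptake or cause-specific mortality. The point is worth correcting because the remedy uses data already listed, but it does not threaten the feasibility conclusion.

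**What to change.** In Statistics and data analysis, amend the control definition as follows.

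1. Apply to controls the same GOLD obstruction criterion that participants must meet, using the SafeHaven lung function results already listed under EHR data.
2. Prespecify the secondary clinical comparisons twice: in spirometry-confirmed controls and in all coded controls.
3. Report the proportion of coded controls in each cohort with a usable spirometry record.

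If the separately registered control component already contains such a criterion, stating it in the protocol covers the first item.

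The cost is one filter on data already to be extracted, and a second run of the comparisons. It is best set when the cohorts are drawn, since the linked data are de-identified and later confirmation from case notes may not be possible. The downside is fewer controls and selection towards patients who have been tested. How severe that is cannot be judged beforehand, because the protocol does not say how complete SafeHaven spirometry is. Reporting both comparisons lets the reader see whether the result depends on the choice.
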